#### 4. *Demographic Baseline Survey*

Prior to implementing the trial, it will be important to more fully characterize the health indicators on Lombok (i.e. MMR, MMRT and IMR) and to establish the geographic heterogeneity of such indicators. As mentioned, there are 3 distinct climatic zones with substantial heterogeneity in agricultural patterns and health seeking behavior. Additional peculiarities, such as the migration of pregnant women to their parents' house for delivery and postpartum recovery, will also be characterized. For these reasons, and to most efficiently coordinate logistics during the trial implementation phase, we will first establish a baseline demographic surveillance system for birth, death, and migration of all pregnant women and women of childbearing age (i.e. 15-45 years, as defined by the National Family Planning Board, Indonesia). This will subsequently be expanded to include children born to these women, and will eventually include other household

children and adults. This phased-in procedure prioritizes pregnant women and their children and allows estimation of several important characteristics of the trial population, including:

1. Maternal mortality ratio (MMR), and maternal mortality rate (MMRT)
2. Inter-village migration of pregnant women
3. Household composition
4. Infant mortality rate

Demographic surveillance will begin 6 months prior to the beginning of the supplement distribution and will be updated at three-month intervals during the project period. This surveillance period prior to intervention will allow estimation of maternal mortality ratio within each of the three climactic zones to within  $\pm 20$ -27% (assuming an overall MMR range of 400 to 800 per 100,000 live births estimated for approximately 10,000 births per zone), and permit determination of infant mortality rates to within  $\pm 7\%$  in each of the three zones. This demographic database will also be linked to the HKI Nutritional Surveillance System (NSS) database, allowing the trial to track a variety of socio-economic, community and familial issues which may be associated with maternal and infant health and mortality.

## *5. Enrollment of pregnancies*

At the onset of the supplement distribution period, pregnant women reporting to a midwife or a midwife's assistant will be enrolled into the intervention if informed consent is given. When reported to the assistant, the woman will be referred to see the midwife as soon as possible. At the time of the first visit to the midwife, the pregnancy will be confirmed by means of a urine test, or physical examination, depending on the estimated gestational age. Based on existing midwife records, we anticipate that pregnancies will be reported between 3-5 months of gestation. Reporting may be earlier once the community knows about the urine test to confirm pregnancy and about the distribution of the supplements.

Because the trial relies exclusively on pregnant women actively seeking antenatal care from the village midwife, improved midwife-seeking behavior will be important. Before the start of the trial, the midwives will be motivated to recruit three to six women in their village to assist the midwife in her trial-related tasks. The role of these assistants is to facilitate identification and enrollment of pregnant women, distribute supplements, and report complications of delivery and maternal death to the midwife. A campaign to encourage early first visits to the midwives will also be conducted in the start-up phase of the trial. The purpose of this social marketing activity is to promote early first visits, promote the use of supplements and to promote the services of the village midwife and her assistants.

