## **SUMMIT activity design and methodology**

*Outcomes:* The SUMMIT activity is a controlled trial designed to assess the relative impact of a prenatal multi-micronutrient tablet in comparison to the current MOH iron/folate tablet on frequency of maternal mortality as assessed by both the maternal mortality ratio (MMR), defined as maternal deaths per 100,000 live births, and the maternal mortality rate (MMRT), defined as the death of a woman while pregnant or within 42 days of termination of pregnancy from any cause aggravated or related to the pregnancy, expressed per 100,000 pregnancies. Two additional main outcomes of the SUMMIT activity are proportion of low birth weight infants, and infant mortality, including neonatal mortality. Secondary outcomes to be assessed include maternal morbidity, neonatal development, and nutritional status during pregnancy and lactation. In addition to examining the effect of multi-nutrients, we will document the effect of education and social marketing of the SUMMIT activity by comparing outcome rates in the iron/folate arm of the intervention area to corresponding rates in designated villages where standard prenatal care practice will continue. In a 20% subsample of pregnancies biochemical status for micronutrients, including, iron, zinc, and vitamin A, will be determined.

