### **B. Specific objectives**

The specific objectives will be to determine the relative impact of multi-micronutrient and iron/folate supplements on maternal and infant health, by assessing:

- i. Maternal mortality defined as pregnancy-related deaths per 100,000 live births (MMR), and also pregnancy-related deaths per 100,000 pregnancies within 6 weeks of termination of pregnancy (MMRT)
- ii. Birth weight
- iii. Neonatal and infant mortality
- iv. Maternal morbidity (e.g. hemorrhage, prolonged labor)
- v. Maternal micronutrient status

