| Detectable
reduction
(%) | Total live births (LB) needed |                        |                      |
|-----------------------------------------|--------------------------------------|------------------------|----------------------|
|                                         | NMR=46/1000 LB                | PNMR=64/1000 LB | LBW=15/100 LB |
| 10                                      | 83,012                               | 58,613                 | 22,862               |
| 15                                      | 36,231                               | 25,597                 | 10,016               |
| 20                                      | 20,006                               | 14,142                 | 5,552                |
| 25                                      | 12,561                               | 8,899                  | 3,498                |

As is general practice for community-based trials, a Data Safety and Monitoring Committee will be convened, and trial data will be evaluated after two years. Should documentable reductions be likely, the committee will decide whether the trial should be terminated or extended. For example, if a 20% reduction in MMR is observed in the multi-nutrient group compared to a MMR of 600/100,000 live births in the iron/folate arm, an approximate 6-month extension would be needed to demonstrate statistical significance.

Sample size determinations are needed for the evaluation of the impact of activities, such as promotion of prenatal care and nutrition, accompanying the supplement distribution. Through the baseline demographic surveillance and continued monitoring of maternal and infant mortality as the intervention is phased in, we propose to document the effect of the activities associated with program implementation on maternal and infant mortality. This will be estimated by comparing MMR, MMRT, and IMR between the non-intervention areas and the iron/folate arm of the intervention area. For the non-intervention area we estimate that maternal and infant mortality rates will be estimated for 54,000 pregnancies. This will be compared to the rate obtained for the iron/folate arm of the intervention for 63,000 pregnancies. This will enable detection of at least a 20-25% (power=80% with  $p<0.05$ ) effect of the program implementation, independent of the multi-micronutrient impact.

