## *12. Data management and analysis*

The first check of the forms will be performed in the field by the field supervisors. Data entry will be done using the *SPSS for Windows* program. Data will be entered in batches, and 10% of each batch will be cross-checked by data-entry supervisors. Batches for which unacceptable error rates are obtained will be re-entered and checked until acceptable

quality standards are met. The data-entry program will prohibit entry of invalid or impossible values and generate a query for follow-up. After data have been entered, additional outliers will be identified and checked against the original questionnaires. Queries regarding unclear or incomplete data will be referred to the field for appropriate follow-up. This system has been field-tested by the HKI NSS and functions well. Primary analyses will compare key outcome event rates event rates, MMR, MMRT, PNMR, and LBW in the multi-micronutrient group with the iron/folate group. However, the SUMMIT activity will not only provide information concerning the impact of micronutrients on these indicators, but it will also assess the specific impact of activities accompanying the intervention such as promotion of prenatal care and social marketing. This will be done by comparison of event rates in the pre and post-intervention areas for the iron/folate arm. This enables one to individually assess the impact of the various components of the SUMMIT activity on the key health outcomes. Relative cost-benefit analyses can therefore be carried out for the various interventions.

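### The programme-effect comparison of MMRT counts pregnancies by surveillance on one side and by trial enrolment on the other

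*Protocol*

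**What the plan says.** - **The comparison.** In VIII.B.3 (Sample Size) the effect of the accompanying activities is to be estimated by "comparing MMR, MMRT, and IMR between the non-intervention areas and the iron/folate arm of the intervention area". VIII.B.12 (Data management and analysis) describes the same contrast as a "comparison of event rates in the pre and post-intervention areas for the iron/folate arm". It is not a randomised comparison.
- **The denominator.** The Executive Summary (Outcomes) defines MMRT as a rate "expressed per 100,000 pregnancies". MMR is per live birth.
- **Non-intervention side.** VIII.B.3 states that "maternal and infant mortality rates will be estimated for 54,000 pregnancies". VIII.B.4 (Demographic Baseline Survey) lists MMRT among the quantities that demographic surveillance will supply. That surveillance starts six months before distribution and "will be updated at three-month intervals during the project period". No pregnancy test or gestational threshold is given for it.
- **Iron/folate side.** The figure is 63,000 pregnancies, half of the 126,000 to be enrolled. VIII.B.5 (Enrollment of pregnancies) enrols women who report to a midwife or her assistant. The midwife confirms the pregnancy by urine test or physical examination. Existing records suggest reporting at 3–5 months, but "Reporting may be earlier once the community knows about the urine test" and about the supplements. The same section describes a campaign for early first visits and assistants who help to identify pregnancies. VIII.B.7 adds incentives to maximise enrolment.
- **Elsewhere.** The Executive Summary (Sample Size) states the detectable programme difference for MMR only. VIII.B.8 (Data collection) also speaks of mortality ratios when it compares baseline with the iron/folate group.

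**The concern.** The activities being evaluated are also the ones expected to change when, and how completely, pregnancies are registered. A pregnancy registered early can still end in miscarriage or abortion. One registered late, or found at a quarterly update, may enter the count only if it survived that long. If the iron/folate side registers more of these losses per live birth than the surveillance does, its MMRT is lower for the same number of deaths, and the difference would be credited to education and social marketing. Section V says this evaluation will be the basis for a cost-benefit analysis to guide government health budgets, so a false fall would have practical consequences.

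The multi-micronutrient versus iron/folate comparison is outside this point, because both arms enrol in the same way.

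**Working it through.** **1. What the two denominators are.** Inputs: 72,000 pregnancies a year (VIII.B.1), so 18,000 a quarter; six months of baseline, then one third of villages entering in each of three successive three-month intervals (VIII.B.2).

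- Non-intervention: 36,000 (baseline) + 2/3 × 18,000 + 1/3 × 18,000 = 36,000 + 12,000 + 6,000 = 54,000. This matches the plan, so the comparator is pre-intervention time.
- Enrolment: 2 × 72,000 − 18,000 = 126,000, and 126,000 / 2 = 63,000. This also matches.

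**2. The plan's detectable effect.** Two-proportion power with pooled variance, two-sided 0.05, 80% power, 54,000 against 63,000:

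| Baseline per 100,000 | No design effect | Design effect 1.2 |
|---|---|---|
| 400 | 24.3% | 26.4% |
| 600 | 20.0% | 21.8% |
| 800 | 17.5% | 19.0% |

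The stated 20–25% is reproduced for 400–600 without a design effect. The planning figure is not in dispute.

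**3. Change in MMRT with deaths and live births held fixed.** Let L0 and L1 be the registered non-live-birth pregnancies per live birth before and during the intervention. With D deaths and B live births, MMRT = D / [B(1 + L)]. The ratio of intervention to pre-intervention MMRT is therefore (1 + L0) / (1 + L1). For example, 1.05 / 1.15 = 0.913, a fall of 8.7%.

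The last three columns give the chance of a significant reduction with no true effect, for MMR 400, 600 and 800 and no design effect. The rates compared are MMR/(1 + L0) and MMR/(1 + L1). The nominal chance in that direction is 2.5%.

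| L0 → L1 (assumed) | Fall in MMRT | 400 | 600 | 800 |
|---|---|---|---|---|
| 0.10 → 0.15 | 4.3% | 6.6% | 8.0% | 9.4% |
| 0.15 → 0.20 | 4.2% | 6.3% | 7.5% | 8.7% |
| 0.15 → 0.25 | 8.0% | 12.9% | 17.2% | 21.5% |
| 0.05 → 0.15 | 8.7% | 15.5% | 21.0% | 26.5% |
| 0.15 → 0.30 | 11.5% | 22.5% | 31.3% | 39.8% |
| 0 → 0.15 | 13.0% | 31.0% | 43.4% | 54.4% |

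With a design effect of 1.2, the 8.7% row becomes 13.6–22.9% and the 13.0% row 26.7–47.2%.

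Only the 15% allowance for abortions, miscarriage and stillbirths comes from the protocol (VIII.B.3). All values of L0 and L1 are assumptions anchored on it.

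**4. Relative size.** 4.2 / 25 = 0.17 and 13.0 / 20 = 0.65. The assumed shifts are roughly one sixth to two thirds of the effect that the comparison is meant to detect.

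**5. Sensitivity to the numerator.** Section II attributes 11.1% of Indonesian maternal deaths to complications of miscarriage. If the pre-intervention side missed a fraction m of these and the iron/folate side missed none, the ratio is multiplied by 1 / (1 − 0.111m). Starting from 0.913:

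- m = 0.5: 0.913 × 1.059 = 0.967, a fall of 3.3%.
- m = 1: 0.913 × 1.125 = 1.027, a rise of 2.7%.

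The direction therefore depends on death ascertainment as well. A difference of that kind would also affect MMR, but it is a separate mechanism from the denominator.

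**The case against.** The best reply is that a common source exists. Surveillance is island-wide and continues through the project, and Section V says the programme evaluation rests on it. The 54,000 and the 63,000 are both projections from the same 72,000 pregnancies a year, so they do not prove that two registers will be used. This stands as far as it goes: the data for a like-for-like count should exist. But the protocol never says that the iron/folate denominator will come from surveillance, and the 63,000 is half of a figure described as enrolment.

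Three further points stand as limits.

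- No sentence says that the urine test is absent before the intervention. That is inferred from the wording of VIII.B.5, which says only that reporting may become earlier.
- Enrolment depends on women coming forward, so women who miscarry before they present never enter. Quarterly contact with all women aged 15–45 could list as many early losses, or more.
- Earlier registration may add early deaths to the numerator (step 5).

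A reader might infer that MMRT must fall by construction, or by as much as 15%. The documents support neither. The allowance works as a share of pregnancies (102,000 / 0.85 = 120,000), so a 15% fall requires enrolment to register every loss and surveillance none. With enrolment expected at 3–5 months that is implausible, and the allowance includes stillbirths, which a system recording births and deaths is unlikely to miss altogether.

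Finally, a fall in MMRT without a fall in MMR would hint at the artefact. That helps interpretation but does not justify planning a comparison on unlike denominators.

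**Conclusion.** The point holds for one measure in one non-randomised comparison. As written, MMRT in the programme-effect comparison sets a surveillance count of pregnancies against an enrolment count. The protocol expects the programme's own activities to shift the enrolment count, so a registration change cannot be separated from a programme effect.

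A fall in MMRT on the iron/folate side is likelier than a rise, but not certain. The size is not in the document. It is about 4–13% under the registration levels assumed above, with deaths and live births fixed, against a stated detectable effect of 20–25%. At the lower end the chance of a false reduction is about 6–9% instead of 2.5%, which is modest. In the middle of the range (8.0–8.7%) it is about 13–27%.

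The randomised comparison is not affected, and MMR is not affected by this mechanism. This is worth correcting before the comparison is run, but it does not threaten the trial's main result.

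**What to change.** In VIII.B.3, base the maternal part of the programme-effect comparison on MMR. This agrees with the Executive Summary (Sample Size) and with VIII.B.8. Make the matching change in VIII.B.12, and keep MMRT for the randomised comparison.

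If MMRT is to stay in the programme-effect comparison, state that pregnancies and deaths on both sides will be counted from the same island-wide quarterly surveillance, with one common gestational threshold for counting a pregnancy, and not from trial enrolment on one side.

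The denominator should not be restricted to live births and stillbirths. That would exclude women who die undelivered or after a miscarriage or abortion, whom MMRT is meant to capture.

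The cost is a change of wording. MMRT is either lost from this one comparison or needs a separate surveillance-based count there.

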## *6. Randomization to treatment*

As described above, the unit for randomization to treatment will be the geographic area serviced by or assigned to the trained village midwife. All pregnant women living in the village of a particular midwife will receive the same supplement. Each of the 300 midwives in the distribution areas will receive a supply of one of the two supplements. Randomization of supplements to 300 midwives will be carried out by a computer

generated randomization protocol optimized to limit the occurrence of identical codes assigned to adjacent midwives. The prognostic heterogeneity and design effect of the randomization will be assessed at baseline using data collected from the demographic surveillance.

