*Sample Size:* The SUMMIT activity will aim to detect a reduction in both MMR and MMRT of at least 30% with a power of 80% and significance level of 0.05. Current estimates of the MMR in various districts on Lombok range from 400 to 800 maternal deaths per 100,000 live births and randomization for the trial will be by clusters consisting of geographic areas serviced by each of the 300 midwives providing prenatal care. Assuming 400 maternal deaths per 100,000 live births and a 10% loss to follow-up, the trial would require enrollment of 102,000 live birth pregnancies allocated to either an iron/folate or multinutrient supplement to detect a 30% reduction in MMR. Because not all pregnancies result in a live birth, it is estimated that the required sample size be increased an additional 15% to 120,000. This sample size will also allow detection of similar reductions in MMRT. It is proposed that enrollment be phased in over a 6-month period and continue for at least 2 years to accommodate seasonal effects. The phased in implementation along with the approximately 72,000 pregnancies occurring each year throughout the trial area yields a projected enrollment of 126,000 pregnancies. The additional margin of enrollment provides the ability to detect reductions in MMR as little as 22% if ratios approach 800 per 100,000 live births. With regard to low birth weight and infant mortality rates, the projected sample size will allow detection of at least a 10% reduction in low birth weight and infant mortality rates, including neonatal mortality rates. Equally important is determination of the impact of the social marketing and education programs that will accompany the trial implementation in the intervention area. Data concerning outcome variables in the absence of the intervention will be collected during the phase-in period prior to enrollment. This will result in the ability to detect at least a 25% difference in MMR between the iron/folate arm of the intervention area compared non-intervention areas.

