## 2. *Design and Methods*

The proposed SUMMIT activity is a double blind, community-based, cluster-randomized, controlled intervention designed to assess the relative impact of multi-micronutrient supplements compared to iron/folate supplements on maternal mortality, infant mortality and low birth weight. Pregnant women will be randomized to one of approximately 300 clusters defined by the geographic area serviced by a trained midwife. This means that all women attended by a particular midwife will receive the same type of supplement. Clustered randomization was chosen due to the logistical and scientific difficulties associated with individual randomization in large scale longitudinal trials. Pregnant woman will be provided with either a daily multi-micronutrient supplement containing iron, folate, vitamin A, and zinc, along with additional B vitamins, minerals, anti-oxidants (for precise composition, see Appendix 3a), or an identical-looking daily supplement containing 30 mg iron and 400 µg folate. There will be no blank placebo group because iron/folate supplementation distribution to pregnant women is the current policy of the GOI.

The intervention will be preceded by a 6-month baseline demographic surveillance period to estimate area-specific maternal and infant mortality rates. Supplementation will then be phased in step-wise by implementation in 1/3 of the villages over 3 successive 3-month intervals. Women who refuse to be included in the trial and those in the pre-intervention areas will receive the standard GOI iron/folate tablets. The GOI iron/folate tablets will, therefore, not be withdrawn from the island but will only be used for individuals not enrolled in the intervention portion of the activity.

Supplements will be provided free to all women with a confirmed pregnancy, from the first antenatal consultation up to three months postpartum. As a joint activity between HKI and the GOI, the existing government system will distribute the supplements to pregnant women and the government-trained midwives will be involved in monitoring the health impact. HKI project staff will also encourage the midwives to provide maximum supplementation coverage. Additional non-invasive surveillance will be carried out by HKI project staff to allow adequate assessment of compliance and health impact.

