|                                         | MMR=400                                                                   | MMR=600 | MMR=800 |
| 15                                      | 509,635                                                                          | 339,137        | 253,887        |
| 20                                      | 281,023                                                                          | 187,017        | 140,012        |
| 25                                      | 176,230                                                                          | 117,290        | 87,815         |
| 30                                      | 119,865                                                                          | 79,777         | 59,731         |
| 35                                      | 86,232                                                                           | 57,381         | 42,967         |
| 40                                      | 64,581                                                                           | 43,035         | 32,192         |

Assuming a conservative MMR estimate of 400 per 100,000 live births, enrollment of 120,000 pregnancies will allow determination of a reduction in MMR of at least 30% with a power of 80% and significance level of 0.05. Similar reductions in MMRT will also be detectable because such rates are expected to be higher given that deaths prior to a live-birth delivery would be included. Given the estimated 72,000 pregnancies per year in the 300 villages on Lombok, and taking into account the phased in implementation schedule, the SUMMIT activity will plan to enroll 126,000 pregnancies over a 2 year active recruitment period. If MMR and MMRT approach 600-800 per 100,000 live births or pregnancies, which is possible considering the high rates of infant and under-five mortality, the sample size of 126,000 pregnancies will allow determination of a statistically significant reduction in MMR and also MMRT of 22-25%.

For infant mortality it will be important to also determine the age-specific effects on neonatal mortality rate (NMR, birth to 30 day mortality) and post-neonatal mortality rate

(PNMR, 1 to 12 months). The projected sample size and trial duration will allow detection of at least a 10% change in NMR and PNMR. In addition, the study will easily detect a difference of 10% in the proportion of low-birth weight (LBW) infants.

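### The supplement is tied to the attending midwife in one section and to the village of residence in another, so a woman who moves for delivery can be resupplied with the other arm's tablet

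*Protocol*

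**What the plan says.** - **Attachment to the midwife.** VIII.B.2 (Design and Methods) explains the clusters by saying that "all women attended by a particular midwife will receive the same type of supplement".
- **Attachment to residence.** VIII.B.6 (Randomization to treatment) says "All pregnant women living in the village of a particular midwife will receive the same supplement". It adds that each of the 300 midwives is stocked with one of the two supplements.
- **Allocation.** VIII.B.6 describes a computer "generated randomization protocol optimized to limit the occurrence of identical codes assigned to adjacent midwives".
- **Movement.** VIII.B.4 (Demographic Baseline Survey) names as a local peculiarity the "migration of pregnant women to their parents' house for delivery and postpartum recovery". It plans to describe this and to estimate inter-village migration through surveillance.
- **Supply.** VIII.B.7 has women collect a 30-tablet pack each month, until 12 weeks after delivery or pregnancy loss. VIII.B.2 makes the two tablets identical in appearance.
- **Sample size.** VIII.B.3 allows for clustering (20%), loss to follow-up (10%) and pregnancies without a live birth (15%). It has no allowance for crossover.

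No section says which product a woman receives while she stays in another midwife's area, or who hands it to her.

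**The concern.** For a woman who lives in one area and is attended throughout by its midwife, the two sentences agree. For a woman staying with her parents around delivery, they need not. Attachment to the attending midwife points to the product of the receiving midwife. Attachment to the village where she lives points, on a plain reading, to her home product. Neither sentence says that the arm of enrolment governs.

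The supply arrangements make this matter. A woman who outlasts her current pack needs another one, the nearest midwife holds a single product, and because the tablets look the same nobody present would notice a switch. The sample pills that VIII.B.11 collects in some cases, for verification after the trial, can reveal a wrong product but cannot prevent one.

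Switching in both directions pulls the arms together. It would fall late in pregnancy and in the weeks after birth, so it bears on maternal mortality and, through the postpartum weeks, on infant mortality. Birth weight is less exposed, because only tablets taken before birth can affect it. Exposure contrast lost in this way cannot be recovered in the analysis.

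**Working it through.** **1. Reproduce the plan's own figure.** The inputs come from the Executive Summary and VIII.B.3.
- Target: "detect a reduction in both MMR and MMRT of at least 30% with a power of 80% and significance level of 0.05". A two-sided test is assumed, because sidedness is not stated.
- Baseline: "Assuming a conservative MMR estimate of 400 per 100,000 live births", so p1 = 0.0040. A 30% reduction gives p2 = 0.0028.
- Allocation: 1:1 is assumed, consistent with 63,000 of 126,000 pregnancies in the iron/folate arm.

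Per arm, with p̄ = (p1 + p2)/2 and d = p1 − p2:

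n = [1.960·√(2p̄(1−p̄)) + 0.842·√(p1(1−p1) + p2(1−p2))]² / d² = 36,937

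With continuity correction: n' = (n/4)·[1 + √(1 + 4/(n·d))]² = 38,586, or 77,172 in total.

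- 77,172 × 1.2 × 1.1 = 101,867, against 102,000 live-birth pregnancies in the Executive Summary.
- 101,867 / 0.85 = 119,844, against 119,865 in the VIII.B.3 table.

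The plan's arithmetic therefore reproduces on its own inputs.

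**2. Add crossover.** Let c be the share of effective exposure switched, equal in both arms:

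c = (share of women who move) × (chance that the receiving midwife holds the other product) × (share of the effect lost by a woman who crosses)

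The document gives none of these three, so all are assumptions. Examples:
- 5% × 0.5 × 0.5 = 1.25%
- 10% × 0.5 × 0.5 = 2.5%
- 10% × 0.5 × 1.0 = 5%
- 20% × 0.5 × 1.0 = 10%

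With baseline risk p and a true 30% reduction, the arm risks become p(1 − 0.3c) and p(1 − 0.3(1 − c)).

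**3. Results at MMR 400.** The 126,000 planned pregnancies correspond to 126,000 × 0.85 / (1.2 × 1.1) = 81,136 before the allowances, or 40,568 per arm. Power comes from inverting the continuity-corrected formula: replace n by (n' − 1/d)²/n' and solve for the power term.

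| c | Reduction seen | Pregnancies needed for 80% power | Power at 126,000 |
|---|---|---|---|
| 0 | 30.0% | 119,844 | 82% |
| 1.25% | 29.4% | about 125,900 | 80% |
| 2.5% | 28.7% | about 132,500 | 78% |
| 5% | 27.4% | about 147,300 | 73% |
| 10% | 24.7% | about 185,700 | 63% |

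**4. Results at higher baselines.** VIII.B.3 also considers MMR 600 and 800. With the same formula, 126,000 pregnancies and a true 30% reduction, power at c = 10% is 81% at MMR 600 and 91% at MMR 800. It is higher at smaller c.

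**The case against.** The strongest reply is that there is only one rule. VIII.B.2 is explaining clusters defined by geographic area, and VIII.B.6 begins by referring back to that description. A stay at the parents' house is temporary, so a woman still lives in her own village and keeps its product. The protocol tracks migration before and during the trial, partly to organise field logistics, and the field manuals still to be written could hold the supply detail. Counting outcomes by enrolment cluster could sit in the statistical analysis plan, which is not at hand.

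Much of this stands, and it limits the point. A reader might infer that both sentences send a mover to the receiving midwife's product. The residence wording does not support that; only the attendance wording does.

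A reader might also infer that the neighbour constraint creates the problem and should go. The documents do not support that either. They do not say that code means arm or that parental homes lie in adjacent areas, and the constraint only limits identical codes. Under plain 1:1 allocation about half of moves would reach the other arm anyway, and spatial alternation buys geographic balance. Keeping it or not is a design trade-off.

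The reply does not remove the conflict. The attendance wording is in the protocol, a midwife can follow it as written, and nothing tells her to do otherwise for a visitor. Tracking migration measures the problem without preventing it. Which product a mover is handed is a matter of trial conduct that the protocol already addresses, in two ways that differ.

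**Conclusion.** The point holds as an inconsistency that should be reconciled. Followed as written, the VIII.B.2 rule lets a woman who moves for delivery be resupplied from the other arm, and the protocol itself expects such moves.

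The size cannot be read from the document. It rests on assumed values for how many women move, where they go and how much of the effect a late switch removes, and on equal crossover in both arms. Under those assumptions the margin above 120,000 is thin at MMR 400: 1.25% effective crossover uses it up, and 2.5% to 5% costs roughly 4 to 9 points of power. At MMR 600 to 800 the 30% target keeps at least 80% power throughout the range examined.

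Two further inferences are not supported. One is that the trial is underpowered: the sample size reproduces, and no mover share is given. The other is that most maternal deaths fall in the exposed window. The cause-of-death table in Section II lists causes and not timing, so adding up hemorrhage, sepsis and prolonged labor does not give that share.

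**What to change.** Reconcile VIII.B.2 and VIII.B.6 into one rule: the allocation code is set by the midwife area in which the woman lives at enrolment, and it stays with her for that pregnancy. To make the rule workable:
- record the code on her card;
- supply movers under that code, for example with sachets handed over before departure;
- instruct receiving midwives not to issue the other code to a woman already enrolled;
- count her outcomes, and her infant's, in the enrolment cluster.

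The neighbour constraint can stay. It is enough to note that, if code means arm, it may raise crossover for short moves.

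The cost is a wording change, a code on the card and modest logistics for movers. No change to the sample size is asked for. The inter-village migration estimate from the baseline surveillance can replace the assumed mover share above once it is available.
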